# Protocol for a randomized, double blind, placebo controlled, crossover trial of Melatonin for treatment of Nocturia in adults with Multiple Sclerosis (MeNiMS)

**DOI:** 10.1186/s12883-017-0845-y

**Published:** 2017-03-27

**Keywords:** Multiple Sclerosis, Nocturia, Melatonin, LUTS, Cognition

## Abstract

**Background:**

Nocturia (the symptom of needing to wake up to pass urine) is common in progressive Multiple Sclerosis (MS) patients. Moderate-to-severe nocturia affects quality of life, can exacerbate fatigue and may affect capacity to carry out daily activities.

Melatonin is a natural hormone regulating circadian cycles, released by the pineal gland at night-time, and secretion is impaired in MS. Melatonin levels can be supplemented by administration in tablet form at bedtime.

The aim of this study is to evaluate the effect of melatonin on mean number of nocturia episodes per night in MS patients. Secondary outcome measures will assess impact upon quality of life, urinated volumes, lower urinary tract symptoms (LUTS), cognition, sleep quality and sleep disturbance of partners.

**Methods:**

A randomized, double blind, placebo controlled, crossover trial consisting of two, six week treatment phases (active drug melatonin 2 mg or placebo), with a 1 month wash-out period in between.

The primary outcome (change in nocturia episodes per night) in this two arm, two treatment, two period crossover design, will be objectively measured using frequency volume charts (FVC) at baseline and following both treatment phases. Questionnaires will be used to assess quality of life, sleep quality, safety and urinary tract symptoms. Qualitative interviews of participants and partners will explore issues including quality of life, mechanisms of sleep disturbance and impact of nocturia on partners.

**Discussion:**

This study will evaluate whether melatonin reduces the frequency of nocturia episodes in MS patients, and therefore whether ‘Circadin’ has the potential to reduce LUTS and fatigue, and improve cognition and overall quality of life.

**Trial registration:**

(EudraCT reference) 2012–00418321 registered: 25/01/13. ISRCTN Registry: ISRCTN38687869

## Background

Normal urinary function shows a circadian (day/night) cycle, with reduced urine production and bladder excitability during sleep. Nocturia is the symptom of needing to wake up to pass urine. It is caused by increased bladder excitability, impaired salt/fluid handling and endocrine causes.

Nocturia is common; overall prevalence of nocturia is substantial, and progresses in severity with ageing [1]. Nocturia is highly prevalent in neurological disease. Mild nocturia (1 episode per night) may be regarded as a “nuisance” symptom, of minor importance. However, if there are other reasons for sleep disturbance, as is common in multiple sclerosis (MS) [2], the additional episode of sleep disturbance from nocturia becomes more important for the person affected.

Moderate-to-severe nocturia profoundly affects quality of life as a consequence of fatigue, which results from the shortening of overall sleep duration and disruption of the phases of sleep (loss of the restorative phase). More importantly, severe nocturia is associated with major health problems [3]. The condition is thus important personally (impaired quality of life from fatigue), economically (impaired function affecting employment; for disabled or elderly people, need for additional care and reduced ability to maintain independent living at home) and clinically (association with major health issues).

Standard treatment comprises controlling fluid intake, timed diuretics, desmopressin, antimuscarinic drugs or bedtime sedatives/miscellaneous compounds [4]. Nocturia can be multifactorial, and a range of interventions is needed to individualise treatment selection and have the best chance of ameliorating symptoms. Current options can have side effects- which are common with antimuscarinics (dry mouth, constipation, swallowing difficulty, cognitive impairment), and sedatives (confusion, sedation hangover). Serious complications include; hyponatraemia (salt depletion/dilution) with diuretics/desmopressin, and acute retention of urine with antimuscarinics. Perceived poor efficacy and the safety concerns mean that clinicians may fail to evaluate fully or feel reluctant to instigate treatment; as a consequence, even severe nocturia symptoms may be left untreated.

Our conjecture is that nocturia signifies impaired circadian regulation, potentially mediated at 3 levels; (i) bladder muscle excitability, (ii) renal urine output, (iii) conscious response to bladder sensation. The concept that nocturia represents a disruption of circadian control of various body processes (bladder urine storage, kidney urine production and brain response to urinary sensation) is evident. It shifts emphasis from organs to the individual person; thereby the treatment basis moves from suppressing organ activity (antimuscarinics, antidiuretics, sedatives), towards restoration of deficient circadian activity. This shift takes a holistic approach aiming to restore normal function in the organism, rather than suppressing abnormal function in individual organs; improved function by restoration of the native hormone. Melatonin is a natural hormone regulating circadian cycles, released by the brain’s pineal gland at night-time, and varying with sleep state. It reduces smooth muscle activity including in the bladder [5]. Melatonin levels can be supplemented by administration in tablet form [6]; given at bedtime, it improves sleep quality. Literature review shows melatonin has been used for nocturia in two small studies. In men with benign prostate enlargements, a subgroup of patients who benefitted from exogenous melatonin treatment (“nocturia responders”) has been reported [7]. Melatonin has also been used for nocturia in the elderly [6], for whom it was found to have significant benefit in ameliorating symptom severity and improving quality of life.

MS is the commonest cause of acquired neurological disability in young adults and is characterised by the progressive inflammatory loss of myelin and neuronal tissue in the central nervous system. In both the initial Relapsing-Remitting Phase and subsequent Progressive Phase of MS urinary symptoms are common, including nocturia, along with sleep disturbance from other causes (e.g. restless legs syndrome, anxiety). The impact upon quality of life is substantial; fatigue leads to reduced capacity to carry out daily activities, which is a particular problem in a disabled patient group. Fatigue itself is the most common symptom of Multiple Sclerosis and the main disabling feature for many patients. There is an absolute paucity of effective therapies for this severe symptom which is considered to be multifactorial and greatly exacerbated by all forms of sleep deprivation and disturbance. Fatigue is well recognised as a key determinant in a patient’s capacity to maintain occupation, independence and social participation.

Impaired melatonin secretion occurs in multiple sclerosis [8, 9]. Melatonin may have anti-inflammatory and neuroprotective effects [10–12], which are potentially relevant when considering its use in MS. We propose that exogenous administration of melatonin may counteract symptom severity in nocturia, with lower risk of adverse effects than current available agents. Accordingly, the main hypothesis is that bedtime administration of a 2 mg melatonin sustained-release tablet will improve clinical nocturia with consequent benefit for sleep quality and quality of life, in patients with progressive MS.

## Study aims

The primary aim is to evaluate effect of melatonin on mean number of nocturia episodes per night.

Secondary aims are to evaluate; 1) Improvement in quality of life, 2) safety, 3) lower urinary tract symptoms (LUTS), 4) total voided (urinated) volume and mean volume per void, 5) sleep quality and 6) sleep disturbance of partners. A sub-group of volunteers will also participate in assessments of Cognition.

## Methods

### Study design

This trial is a double-blind randomised placebo controlled crossover clinical trial to compare sustained-release melatonin (‘Circadin’ 2 mg) against placebo. A run-in phase will be followed by two treatment phases (active drug or placebo) of 6 weeks each separated by a wash-out interval of 1 month.

The treatment phases will be 2 mg per night (taken at bedtime) of capsulated sustained-release melatonin (‘Circadin’) or 1 placebo capsule per night, identical in appearance to ‘Circadin’; order of administration will be double-blind randomized.

Return to baseline after washout between the two treatment phases will be assessed with the International Consultation on Incontinence-Nocturia (ICIQ-N) and Cambridge Multiple Sclerosis Basic Score (CaMBS).

### Study setting and participants

This trial will recruit multiple sclerosis patients from North Bristol NHS Trust. Eligible subjects must be over 18 years of age with a confirmed neurological diagnosis of MS and least 1 episode of nocturia (as defined by International Continence Society criteria [13]) every night. In addition female subjects of child-bearing potential must agree to use an effective method of contraception throughout the study.

Subjects will be excluded if they i) are pregnant, ii) have a symptomatic urinary infection or iii) indwelling catheter, iv) use prescription/non-prescription sleeping tablets or Melatonin, v) use desmopressin or investigational medical compounds in the month preceding randomization vi) take antimuscarinic or diuretic medication, unless used long-term prior to study (at least 3 months) and continued at same dosing regime throughout the study, vii) have Diabetes mellitus or Diabetes insipidus.

All subjects will provide informed written consent prior to involvement in the study. The NRES Committee South West – Exeter have approved the study protocol (REC reference number: 12/SW/0322). A request for a clinical trial authorisation was accepted by the UK MHRA (reference; 18524/0222/001-0001). The study is registered in the BioMed Central ISRCTN Registry (http://www.isrctn.com/ISRCTN38687869).

Any protocol modifications that become necessary during the course of the trial will be discussed with all relevant parties in advance.

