### Withdrawal criteria

A study subject will be discontinued from participation in the study if:Any clinically significant Adverse Event (AE) as evaluated by the PI, laboratory abnormality, intercurrent illness, or other medical condition or situation occurs such that continued participation in the study would not be in the best interest of the subject.The subject meets any exclusion criterion (either newly developed or not previously recognized).

Subjects are free to withdraw from participation in the study at any time upon request. Subjects who withdraw from the study will be followed up clinically as part of normal clinical care. Patients who withdraw as a consequence of Adverse Events will be followed up by the Study for 3 months and remain under clinical management thereafter if indicated. Safety data will be collected on any subject discontinued because of an AE or Serious Adverse Event (SAE) for a period of 3 months. Every effort will be made to undertake protocol-specified safety follow-up procedures under medical supervision until the symptoms of any AE resolve or the subject’s condition becomes stable. If voluntary withdrawal occurs, the subject will be asked to continue scheduled evaluations, complete an end-of-study evaluation, and be given appropriate care. All trial data to date will be held securely as per study subjects completing the protocol.

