### Randomisation and enrolment procedure

Patients will be enrolled by invitation, if they fulfil all inclusion criteria and no exclusion criteria. A randomisation schedule will be generated by the website Randomization.com (http://www.randomization.com). Clinical trial materials will be packed and Qualified person (QP) certified by a contracted NHS Pharmacy, according to the randomization schedule (under Article 13 of EU directive 2001/20/EC). The medication bottles and randomization schedule will be shipped to the site pharmacy, following regulatory approvals. The randomisation schedule will be strictly controlled and remain in the pharmacy site file for emergency unblinding purposes. These features ensure the study has pharmacy controlled allocation concealment. Medication bottles will be dispensed in sequential number order, with each subject receiving Period 1 and Period 2.

Unblinding during the trial will only be undertaken in the event of a SAE or Suspected Unexpected Serious Adverse Reaction (SUSAR), or disease progression, under the authorization of the principal investigators. Emergency unblinding will be managed by North Bristol NHS Trust Pharmacy Department, according to standard operating procedure (CT/011). The study includes three MS-specific Expanded Disability Status Scale (EDSS) tests (pre-treatment and at the end of each treatment period) to monitor disease severity. Interim analysis will evaluate outcomes of the first treatment period. The analyses will provide the content of a blinded report to the Trial Management Group (TMG). If issues of safety emerge, the TMG will be empowered to request unblinded data.

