### Interaction with other drugs

The subjects will not be permitted to useSedative medications (CNS depressants). Taking melatonin along with sedative medications might cause excessive sleepiness. Sedative medications include clonazepam (Klonopin), lorazepam (Ativan), phenobarbital (Donnatal), zolpidem (Ambien), and others. Patients will be instructed to discuss with the trial co-ordinating office before starting such medications.

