Caution will be advised for the following;Birth control pills (Contraceptive drugs). Taking melatonin along with birth control pills might increase the effects and side effects of melatonin. Effective methods of birth control for females of child-bearing potential are an inclusion criterion of the MeNiMS study; the trial co-ordinating office records method of contraception on the Case Report Form (CRF).Fluvoxamine (Luvox). Taking fluvoxamine (Luvox) can increase the amount of melatonin that the body absorbs. Taking melatonin along with fluvoxamine (Luvox) might increase the effects and side effects of melatonin. Patients will be instructed to discuss with the trial co-ordinating office before starting fluvoxamine.Medications for diabetes (Antidiabetes drugs). Melatonin might increase blood sugar, and thereby might decrease the effectiveness of diabetes medications. The dose of diabetes medication might need to be changed. Some medications used for diabetes include glimepiride (Amaryl), glyburide (DiaBeta, Glynase PresTab, Micronase), insulin, pioglitazone (Actos), rosiglitazone (Avandia), chlorpropamide (Diabinese), glipizide (Glucotrol), tolbutamide (Orinase), and others.Medications that decrease immune system function (Immunosuppressants). Melatonin might reduce the efficacy of immunosuppression. The trial co-ordinating office will discuss immunosuppression therapy with relevant patients.Medications that slow blood clotting (Anticoagulant/Antiplatelet drugs). Melatonin might slow blood clotting. Taking melatonin along with medications that also slow clotting might increase the chances of bruising and bleeding. Some medications that slow blood clotting include aspirin, clopidogrel (Plavix), diclofenac (Voltaren, Cataflam, others), ibuprofen (Advil, Motrin, others), naproxen (Anaprox, Naprosyn, others), dalteparin (Fragmin), enoxaparin (Lovenox), heparin, warfarin (Coumadin), and others. The trial co-ordinating office will discuss anticoagulation therapy with relevant patients.Nifedipine GITS (Procardia XL). Taking melatonin might decrease the effectiveness of nifedipine GITS for lowering blood pressure.Verapamil (Calan, Covera, Isoptin, Verelan). Verapamil (Calan, Covera, Isoptin, Verelan) can increase how quickly the body metabolises melatonin. Taking melatonin along with verapamil (Calan, Covera, Isoptin, Verelan) might decrease the effectiveness of melatonin.

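### The sleeping-tablet exclusion is narrower than the on-study ban on sedatives, so a patient can be eligible on a drug the protocol forbids

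*Protocol article*

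**What the plan says.** The article has one rule for entry and another for conduct on study.

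- **Entry.** Exclusion iv, under Study setting and participants, covers those who "use prescription/non-prescription sleeping tablets or Melatonin". None of exclusions i to vii names sedatives or CNS depressants as a class. Under Randomisation and enrolment procedure, "Patients will be enrolled by invitation, if they fulfil all inclusion criteria and no exclusion criteria".
- **On study.** Interaction with other drugs states: "The subjects will not be permitted to useSedative medications (CNS depressants"). It continues: "Sedative medications include clonazepam (Klonopin), lorazepam (Ativan), phenobarbital (Donnatal), zolpidem (Ambien), and others". The reason given is safety: "Taking melatonin along with sedative medications might cause excessive sleepiness". The only handling instruction is "Patients will be instructed to discuss with the trial co-ordinating office before starting such medications".
- **Other interacting drugs.** The rest of that section opens with "Caution will be advised for the following" and bans nothing further.
- **Discontinuation.** Under Withdrawal criteria, one of the two triggers is "The subject meets any exclusion criterion (either newly developed or not previously recognized"). The other is a best-interest judgement.
- **Screening.** Planned interventions lists a medication review in the baseline clinical assessment and attaches no rule on sedatives to it.

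**The concern.** The exclusion is defined by what the drug is used as (a sleeping tablet). The ban is defined by drug class, whatever the indication. The second set is larger than the first, and the difference is made up of sedatives taken for something other than sleep. A patient in that group satisfies every entry criterion and then cannot follow the protocol on the current drug.

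What is at stake is safety and orderly conduct, not the statistics of the primary comparison. The protocol itself says the combination may be harmful. A conflict that could be settled at screening may instead come up after enrolment, when a medicine prescribed for another condition would have to be stopped or changed for the sake of the trial. If it is not stopped, the patient is in breach of the protocol.

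**Working it through.** No arithmetic is needed beyond a count; the check is a side-by-side reading of the rules.

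1. **Scope of the two rules.** Exclusion iv covers sleeping tablets and melatonin. The ban covers sedatives (CNS depressants), with an open-ended list of four named drugs. Nothing in the interaction section limits the ban to use for sleep.

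2. **A test case.** Take a candidate on clonazepam, lorazepam or phenobarbital for a non-sleep indication, who otherwise qualifies. Exclusion iv is not met, since the drug is not taken as a sleeping tablet. No other exclusion applies. By the enrolment rule this candidate may be enrolled. By the ban, the candidate may not use the drug as a subject. The only ways out are to stop the drug, change it, or breach the ban.

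3. **Whether another section settles it.**
   - The handling instruction in the interaction section concerns starting such drugs, not existing use.
   - The medication review lets staff see the drug, but no listed criterion makes it a ground for exclusion.
   - The automatic route under Withdrawal criteria refers back to the exclusion criteria, which this use does not meet.
   - The best-interest clause there, and the clinician's freedom under Regulatory issues to give other treatment, allow individual judgement but state no rule for existing sedative use at entry.

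4. **How other existing drug use is treated.** Exclusion vi deals with antimuscarinics and diuretics already in use: they are allowed if taken for at least 3 months and continued unchanged. Exclusion v deals with desmopressin in the month before randomisation. So the exclusion list is where the protocol normally settles existing drug use.

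5. **Count in the interaction section.** Not permitted: 1 class (sedatives). Caution only: 7 groups (birth control pills, fluvoxamine, antidiabetes drugs, immunosuppressants, anticoagulant/antiplatelet drugs, nifedipine GITS, verapamil). The single forbidden class is only partly carried into the entry criteria.

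6. **Plausibility.** The Background names restless legs syndrome and anxiety as causes of sleep disturbance in MS, so patients with conditions other than insomnia are expected. The document gives no figures on how many take a sedative.

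**The case against.** The strongest reply is that the two rules do different jobs and do not contradict each other. An entry criterion and a list of prohibited medication apply together, and nothing in the article permits what the ban forbids. Meeting the criteria is a condition for being invited; it does not oblige staff to enrol someone who plainly cannot comply. The baseline medication review, the run-in phase and the full explanation before consent all give an opportunity to resolve the matter before study drug is taken. The instruction about starting sedatives suggests the authors assumed subjects would enter free of them. Finally, a journal article condenses eligibility, and the handling of existing users may be set out in the full protocol.

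Part of this stands. Careful staff may well catch such a patient in time, so it is not certain that the conflict surfaces after enrolment. The probable intention is that users of these drugs stay out. Reading sleeping tablets to mean every sedative would also close the gap, although the text does not say that.

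It does not remove the point. The ban is on use, not only on starting. If the intention was to keep existing users out, exclusion iv is too narrow; if it was to let them in, the ban is worded too widely. Either way one printed sentence needs correction. Nor is this a detail left to a longer document: both rules are printed and their scopes differ.

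**Conclusion.** The concern holds, as a minor matter. Exclusion iv is narrower than the ban it should match, so a patient taking a forbidden sedative for a non-sleep reason is eligible as the criteria are printed but cannot comply without stopping or changing it.

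The conclusion assumes that sleeping tablets carries its ordinary meaning and that the ban applies to the whole class whatever the indication, as written. The number of affected candidates is unknown and could be none. No effect on power, sample size or bias is claimed.

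**What to change.** Keep exclusion iv and extend it to patients who, at the baseline medication review and before randomisation, are taking any other sedative (CNS depressant) barred under Interaction with other drugs, for example clonazepam, lorazepam, phenobarbital or zolpidem.

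Add one sentence to Interaction with other drugs: starting one of these other sedatives during the study remains under the consult-first instruction and does not in itself count as a newly developed exclusion criterion. Without it, the wider exclusion would make every new start an automatic discontinuation under Withdrawal criteria.

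A stable-dose exception modelled on exclusion vi is not a good alternative here, because it would allow the use that the interaction section forbids.

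The cost is a change to one criterion and one added sentence; the medication review is already planned. Some candidates, number unknown, become ineligible, but they could not have complied without stopping the drug. Sedative use present at baseline but discovered only later would lead to discontinuation as a criterion not previously recognised, as for any other exclusion.
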